# Effects of variable frequencies of kinesthesia, balance and agility exercise program in adults with knee osteoarthritis: study protocol for a randomized controlled trial

**DOI:** 10.1186/s13063-021-05386-3

**Published:** 2021-07-21

**Keywords:** Knee osteoarthritis, Exercise training, Knee stability, Pain, Physical function, Proprioception, Quality of life

## Abstract

**Background:**

Knee osteoarthritis (OA) is a common painful and disabling condition that affects older individuals. Proprioceptive training programs in the form of kinesthesia, balance and agility (KBA) exercises have been reported to be beneficial for individuals with knee OA. However, the most optimal training dosage of KBA exercises is still unclear. The aim of this study is to determine the effects of different frequencies of KBA training (i.e., twice-weekly or thrice-weekly) in adults with knee OA.

**Methods:**

A single (assessor) blind, three-arm parallel, multi-center randomized controlled trial will be conducted. One hundred twenty adults with knee OA will be recruited from four tertiary hospitals in Northwestern Nigeria and randomly assigned into one of three intervention groups; twice-weekly KBA (*n* = 40), thrice-weekly KBA (*n* = 40), and conventional physiotherapy (*n* = 40) in the ratio of 1:1:1. Participants in the conventional physiotherapy group will receive two sessions of brief patient education, and sixteen sessions of ultrasound therapy, and stretching and strengthening exercises for 8 weeks. Participants in the two different KBA groups will receive KBA training according to the designed sessions for 8 weeks in addition to the conventional physiotherapy program. All groups will be assessed pre-intervention, immediately post-intervention and at 3 months, 4 months, and 6 months post-randomization. The primary outcome will be physical function (Ibadan Knee and Hip Osteoarthritis Outcome Measure) whereas the secondary outcomes will be pain intensity (Visual Analogue Scale for pain), knee stability (Knee Outcome Survey-Activities of Daily Living Scale), proprioception (electronic goniometer), and quality of life (Osteoarthritis Knee and Hip Quality of Life Questionnaire).

**Discussion:**

The findings of this study may provide evidence on the effectiveness of KBA exercise training and the ideal number of sessions needed to achieve the highest effectiveness in adults with knee OA.

**Trial registration:**

Pan African Clinical Trials Registry (PACTR201810713260138). Registered on 28 November 2017.

**Supplementary Information:**

The online version contains supplementary material available at 10.1186/s13063-021-05386-3.

## Background

Osteoarthritis (OA) is a common chronic degenerative joint disorder that affects people particularly the older population [1]. It is considered to be a disorder of dynamic pathology typified by progressive loss of articular cartilage, subchondral bone sclerosis, cyst, and osteophyte formation [2]. The impact of OA is multifactorial including pain, reduced physical function and quality of life, as well as increased healthcare and socioeconomic cost [3–5]. OA is the leading cause of disability worldwide [6]. About 250 million people are currently affected by OA, and the burden of this disorder is expected to rise globally over the coming decades perhaps due to the combined effects of the aging and obesity epidemic, along with increasing numbers of joint injuries [3].

The knee is one of the most commonly affected joints and accounts for the majority of disability from OA particularly in the elderly [7]. Epidemiological data suggest that about 14 million US populations have symptomatic knee OA, and more than half of these individuals are less than 65 years old [8]. Although data on the prevalence of knee OA in Africa is somewhat sparse [9], numerous hospital-based studies in Nigeria have indicated that knee OA is common [10–14], with prevalence rates of 19.6–20.6% in people ≥ 40 years old [10, 11] and 16.3% in people ≤ 30 years old [11]. Moreover, female gender, advanced age, obesity, knee malalignment, previous knee injury, and decreased quadriceps strength were reported to be the common risk factors associated with knee OA in Nigeria [11, 13–15] as found in the western nations [5, 16, 17].

Knee OA poses a major health problem to the society as it accounts for more walking disability than any other condition [18]. Though to date, no specific cure for OA exists, current treatment methods including pharmacological, non-pharmacologic and surgical modalities are targeted at reducing symptoms, minimizing functional disability, and limiting disease progression [19]. Non-pharmacological methods such as education/self-management, exercise, weight loss if overweight or obese, walking aids as indicated, and thermal modalities are recommended as first-line treatment [20]. These modalities are commonly prescribed for individuals with mild to moderate knee OA.

Exercise therapy is probably the most widely prescribed intervention for knee OA. Evidence suggests that exercise therapy, even though its effects are modest, is beneficial for individuals with knee OA [21, 22], hence universally endorsed by many treatment guidelines [23–27]. The most recent systematic review and meta-analysis found high-quality evidence that land-based exercise programs provide positive benefits for pain and quality of life and moderate-quality evidence of improved functional disability in individuals with knee OA [21]. While several forms of exercise interventions for this disabling condition exist, most conventionally fall into strengthening, aerobic, flexibility and skills/balance or proprioceptive exercises [28].

Proprioceptive exercises are commonly prescribed for individuals with knee OA, with the goals of improving joint proprioceptive acuity (position sense and motion sense [kinesthesia]) and dynamic stability [29] as these components are commonly altered in these individuals [30–33]. Moreover, there is evidence to suggest that proprioceptive training performed in both weight-bearing and non-weight-bearing positions can enhance proprioceptive acuity, and reduce pain as well as functional disability in individuals with knee OA [29, 34, 35].

Kinesthesia, balance and agility (KBA) is a form of proprioceptive training that has been gaining interest among researchers in the management of knee OA and knee-related injuries. This exercise training is typically designed to improve dynamic joint stability and neuromuscular control using a series of physical activities that challenge the individual’s neuromuscular system to maintain balance and coordination [36]. KBA techniques are commonly used in the rehabilitation and prevention of knee ligamentous injury [37–40] and ankle instability [41, 42]. However, in recent years, KBA has been also applied in the management of individuals with knee OA. The benefits of this intervention in knee osteoarthritic condition were first reported in a case study of a physically active, elderly woman with bilateral knee OA [43]. After receiving a 6-week, twice-weekly KBA plus therapeutic exercise program, the patient’s symptoms resolved rapidly and was able to return to recreational sports.

So far, to our knowledge, only six randomized controlled trials (RCTs) [36, 44–48] investigated the effects of KBA exercises  among individuals with knee OA. Two trials [36, 44] applied 8 weeks, three times per week of KBA plus resistance training, and found no superior benefits of this combination on Western Ontario and McMaster Universities Osteoarthritis Index (WOMAC) pain and physical function compared to resistance training alone. A similar result was also reported in another trial [45] that applied 6–8 weeks, two times per week of KBA plus resistance training. On the contrary, superiority results were reported with 8 weeks, three times per week of KBA plus resistance training compared to resistance training alone in one [46] of the earlier trials. This is also in line with another earlier trial [47] that found higher positive effects of KBA training alone on perceived pain and functional capacity when compared to non-treatment. However, when the treatment sessions of KBA training were increased to five times per week for 4 weeks [48], no superiority effects were observed over strength training on perceived pain and most symptoms. While the results of these studies are promising, the question of what is the ideal number of sessions (dosage) of structured KBA exercises that can be expected to produce the desired therapeutic outcomes however remains to be addressed. Moreover, no study has combined or compared KBA training with a conventional physiotherapy consisting of education/self-management, thermotherapy, and stretching and strengthening exercises among individuals with knee OA despite these methods are endorsed as the first-line management [20].

It is conceivable that the small to moderate effect sizes detected in exercise-based RCTs on knee OA may be due to insufficient dose used [20]. It has recently been suggested that evidence-based proprioceptive training should consider training frequency of at least three times per week, for 30 to 40 min per session to achieve the highest effectiveness [34]. The frequency and number of sets to be performed therefore should be taken into consideration when designing proprioceptive-based training programs for knee OA individuals as these exercise programs may appear challenging especially among older individuals. Thus, this study will be conducted to determine which frequency of structured KBA exercise training (i.e., twice-weekly or thrice-weekly) will produce superior therapeutic outcomes in adults with knee OA. The primary outcome will be physical function whereas secondary outcomes will be pain intensity, knee stability, proprioception, and quality of life.

## Methods

### Study design

This study will be a single (assessor) blind, three-arm parallel, multi-center RCT. The outline of the study protocol is shown in Fig. 1. The protocol for this study is reported in accordance with the Standard Protocol Items: Recommendations for Interventional Trials (SPIRIT) 2013 Checklist (Additional file 1).

**Fig. 1 Fig1:**
[figure not shown]
The outline of the study protocol.

### Study setting

The study will be conducted at four tertiary hospitals in Kano city, Kano State, Northwestern Nigeria; Muhammad Abdullahi Wase Teaching Hospital (MAWTH), Murtala Muhammad Specialist Hospital (MMSH), Aminu Kano Teaching Hospital (AKTH), and National Orthopedic Hospital Dala (NOHD). These centers were chosen to have the required number of participants.

### Training of physiotherapists/research assistants

Prior to the commencement of the study, two licensed physiotherapists with at least 2 years of clinical experience will be recruited as research assistants in each of the four hospitals. One physiotherapist will be responsible for eligibility and outcome (baseline and follow-up) assessments. This physiotherapist will be blinded to group allocation. The other physiotherapist will be responsible for treatment. All the physiotherapists will receive a 2-day training on the study procedures by the lead investigator ([name]).

### Participants’ recruitment and eligibility

Participants for this study will be consecutive patients with knee OA referred to the physiotherapy department by the general practitioners in the four tertiary hospitals. Also, recruitment adverts using local posters with the contact of the primary investigator will be pasted at various notice boards in the selected hospitals. To be eligible for the study, participants must meet the clinical criteria for the diagnosis of knee OA according to the American College of Rheumatology (ACR) criteria for unilateral or bilateral symptomatic knee OA [48] in addition to being male or female of 30 to 65 years old. They will be excluded if they have any history of knee, hip, or ankle surgery prior to the study, peripheral vascular disease, local or systemic infection, deformity in lower limbs, rheumatic disease other than OA, high-risk health status for exercise, unresolved balance or neurological disorder, and history of a lower extremity exercise program for a minimum of six weeks prior to enrollment.

### Baseline assessment

 Patients will be assesed for eligibility by the physiotherapists at the four recruiting hospitals through history taking physical examination, and evaluation of self-report questionnaires. After ensuring eligibility, participants will be given oral and written information regarding the procedures and potential risks of the study. Written informed consent will be then sought and obtained. Baseline socio-demographic and clinical variables such as age, gender, marital status, education level, occupational status, height, weight, body mass index, duration of knee pain, and side affected will be collected using a prepared proforma. Baseline self-report outcome assessments will include physical function, pain intensity, knee stability, and quality of life. Baseline objective outcome assessment will be proprioception measurement. The flow of participants is depicted in Fig. 2.

**Fig. 2 Fig2:**
[figure not shown]
The flow of participants

### Randomization and blinding

After completing the baseline assessment, the participants will be randomized into three intervention groups; twice-weekly KBA, thrice-weekly KBA, and conventional physiotherapy (control) in the ratio of 1:1:1. The randomization will be performed using an online randomization generator (http://www.randomization.com) by utilizing block randomization with a block size of 3 and 6. A third party not  involved in the study will perform the randomization process. Allocation of participants will be concealed using consecutive numbered, sealed, and opaque envelopes. The outcome assessors (physiotherapists) will be blinded to the group allocation and will not be involved in administering the interventions. The participants will be told they are in a “twice weekly KBA” or “thrice-weekly KBA” or “conventional physiotherapy,” but the type of intervention will not be specified. Conversely, due to the nature of the interventions, it will be difficult to blind the physiotherapists providing the treatments. Unbinding conditions will be only permissible when there is a medical emergency.

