### Interventions

Participants in the conventional physiotherapy group will receive brief patient education, ultrasound therapy, and stretching and strengthening exercises. The program will be delivered twice weekly for 8 weeks except for the education program which will be provided in two sessions. The stretching exercises will be performed as warm-up and cool-down. Participants in the twice-weekly KBA group will receive two sessions per week of the KBA exercise training for 8 weeks whereas participants in the thrice-weekly KBA will receive three sessions per week of the same exercise training as for the twice-weekly KBA group. Both the two KBA exercise training groups will receive the same intervention program as described for the conventional physiotherapy group prior to receiving the KBA exercise  training. All exercises will be delivered individually under the supervision of the treating physiotherapists. All lower-extremity exercises will be performed bilaterally. The participants will be instructed to perform exercises consistent with their group allocation two times per day at home to encourage self-management. They will be encouraged also to perform a walking exercise of 30 min per day at least 3 to 4 days per week at home. To enhance compliance with the home program, a leaflet with descriptions and pictures of the exercises will be provided to the participants. However, exercises that are more challenging or those requiring the strict supervision of the therapist will be not advised for the home program.

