### Statistical analysis

An independent statistician who will be blinded to the study procedures will conduct all statistical analyses. The normality test of the data will be verified with the Shapiro–Wilk test and visual inspection of distribution plots. To account for potential missing data in datasets, per-protocol (PP) and intention-to-treat (ITT) approaches will be considered for the data analysis. For the PP approach, only participants who completed all treatment sessions will be included in the analysis. For the ITT approach, multivariate imputation by chained equations will be employed [68]. Descriptive statistics of mean and standard deviation will be used to summarize all continuous variables while frequency and percentages will be used to summarize all categorical variables. Mixed between-within subject ANOVA will be used to assess interaction effect (group x time), main effects for time, and between-subjects effect if the data is normally distributed. However, Friedman’s ANOVA and Kruskal–Wallis test will be used to analyze within-group change and between-group difference, respectively, if the data is not normally distributed. Post hoc analysis using Bonferroni correction will be conducted for any significant between-group difference observed. Effect size will be also computed to determine the magnitude of change in outcomes. All data will be analyzed using SPSS version 23 (IBM Co., Armonk, NY, USA) at an alpha level of 0.05.

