## Discussion

There is evidence to suggest proprioceptive deficits in individuals with knee OA and that neuromuscular training programs targeting to improve proprioception are beneficial among these individuals [29–34]. The effectiveness of KBA as a proprioceptive training program in individuals with knee OA has been recently tested in clinical trials [36, 44–48], however, clinicians need to know the ideal dosage of KBA associated with the highest effectiveness as results of these previous trials were mixed. The present study will be aiming to determine the effects of a structured KBA exercise training program with different frequencies of treatment sessions (i.e., twice-weekly or thrice-weekly) on physical function, pain intensity, knee stability, proprioception, and quality of life in adults with knee OA. The outcomes will be evaluated at 8 weeks, 3 months, 4 months, and 6 months after randomization. We hope to follow-up the patients for a year if the 6-month follow-up results suggest this would be useful.

The findings of this study may provide evidence on the effectiveness of the KBA exercise training and the ideal number of sessions needed to achieve the highest effectiveness, which may guide clinical practice and minimize waste of time and resources.

Potential factors that could account for the limitations of the present study may include the lack of blinding of the treating therapists due to the nature of the interventions. Furthermore, because the present study is a multi-center trial employing the services of different treatment therapists with different skills and expertise, we cannot rule out the possibility of differential treatment. However, the assessor blind, three-arm RCT design with concealed allocation can be considered as the strengths of our study.

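### Hospital, treating therapist and assessor are one four-level factor that the stated analysis model omits, at a cost in precision but not in validity

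*Protocol article*

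**What the plan says.** Study setting: "The study will be conducted at four tertiary hospitals in Kano city". Training of physiotherapists/research assistants: "two licensed physiotherapists with at least 2 years of clinical experience will be recruited as research assistants in each of the four hospitals". One of the two assesses eligibility and all outcomes at baseline and follow-up; for the second, "The other physiotherapist will be responsible for treatment". All of them receive the same 2-day training. Interventions: "All exercises will be delivered individually under the supervision of the treating physiotherapists".

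Randomization and blinding gives a 1:1:1 ratio, "utilizing block randomization with a block size of 3 and 6", and numbered sealed envelopes. It does not say whether there is one list for the trial or one per hospital.

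Statistical analysis, for normally distributed data: "Mixed between-within subject ANOVA will be used to assess interaction effect (group x time), main effects for time, and between-subjects effect". Otherwise Friedman's test is used within groups and the Kruskal-Wallis test between groups. Neither route mentions hospital or therapist.

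The Discussion names as a limitation that, with the trial "employing the services of different treatment therapists with different skills and expertise, we cannot rule out the possibility of differential treatment".

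**The concern.** The document names a source of variation, holds the variable that identifies it, and then specifies a model without that variable. With one treating therapist and one assessor per hospital, a four-level hospital factor captures therapist, assessor and local case mix together.

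At stake is how precisely the three arms can be compared on physical function and the secondary outcomes. If patients improve more under one therapist than under another, that difference either falls unevenly on the arms by chance or stays in the error term. Both make the comparison less sharp than the same data allow.

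**Working it through.** **Inputs from the protocol article.** 120 participants in three arms of 40; four hospitals; one treating and one assessing physiotherapist in each; blocks of 3 and 6; five assessments (before and immediately after treatment, and at 3, 4 and 6 months). It states no figure for the effect of hospital, so there is none to reproduce.

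**Assumed.** Equal hospitals (120 / 4 = 30 patients, ideally 10 per arm), and a share s of the relevant variance explained by hospital of 2%, 5%, 10% or 20%.

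**Which variance.** A stable hospital shift, such as an assessor who scores generously at every visit, adds the same constant at each time point and cancels from group x time. For that test, s is the hospital share of the variance of change, and only a hospital x time term can recover it. For the between-subjects effect, s is the share of the variance of the outcome averaged over visits, and the hospital main effect recovers it.

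**Case 1: one list for the trial.** In 20,000 simulated sequences with blocks of 3 and 6 spread at random over four hospitals of 30:
- the median of the largest within-hospital gap between arms is 7 patients;
- a gap of 6 or more (for example 13 against 7) occurs in some hospital in about 73% of trials;
- a gap of 8 or more occurs in about 39%.

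A second simulation, with hospital sizes left to chance, gives a mean largest gap of about 7 (95th percentile 11). Separate lists per hospital would give about 1.4 (95th percentile 2). With one list and no hospital term, simulated type I error is 5.0%, 5.3%, 5.4% and 5.5% at shares of 2%, 5%, 10% and 20%. With 2,500 runs per cell the simulation error is sqrt(0.05 x 0.95 / 2,500) = 0.44 percentage points, so these agree with 5%.

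**Case 2: one list per hospital, hospital left out of the model.** Arms are balanced within hospitals, so hospital variation does not enter the arm difference but is still counted in the residual. The standard error is too wide by 1/sqrt(1 - s), and the loss is equivalent to 120 x s participants:

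| s | 1/sqrt(1 - s) | Standard error wider by | Participants lost |
|---|---|---|---|
| 2% | 1.010 | 1.0% | 2.4 |
| 5% | 1.026 | 2.6% | 6 |
| 10% | 1.054 | 5.4% | 12 |
| 20% | 1.118 | 11.8% | 24 |

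The test is then conservative. Simulated type I error is 3.9% at 10% and 3.2% at 20%; at 2% and 5% it was 4.3% and 5.2%, not clearly different from 5%.

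**Power.** For an assumed pairwise difference of 0.65 SD, comparing no stratification and no hospital term with both in place:

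| s | Neither | Both | Difference (points) |
|---|---|---|---|
| 2% | 83.6% | 83.5% | -0.1 |
| 5% | 82.7% | 84.0% | 1.3 |
| 10% | 82.6% | 85.0% | 2.4 |
| 20% | 84.8% | 89.8% | 5.0 |

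The simulation error of each difference is about sqrt(2 x 0.83 x 0.17 / 2,500) = 1.1 points, so only the gains at 10% and 20% stand clear of noise. With one list kept as it is, adding the hospital term alone gives 84.8% at s = 10% and 89.3% at s = 20%. Most of the gain therefore comes from the model, not from the lists.

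**The case against.** The strongest reply is that this is a journal article. Whether lists are kept per hospital is a detail that the full protocol may hold, and an analysis plan may add covariates. This stands for randomisation. A reader might infer from the text that a single list serves the whole trial, but the section does not say so, and the 73% and 39% figures apply only if it does. It stands less well for the analysis, because Statistical analysis lists the effects to be tested and hospital is not among them.

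A reader might also infer that therapist differences bias the arm comparison or produce false positives. The documents do not support this. Patients at every hospital are allocated to all three arms, so hospital is crossed with arm. Chance imbalance under one list is already reflected in a valid standard error, and under per-hospital lists the error is on the safe side.

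Third, a stable difference between assessors cancels from group x time. This is correct, and it is why a hospital main effect alone would not help that test.

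Fourth, it is tempting to say that adjustment would remove the limitation in the Discussion. It would not. That limitation covers differential treatment, which includes therapists delivering one arm better than another. Hospital and hospital x time absorb average differences between hospitals, not differences by arm. The shared 2-day training is the only stated safeguard against uneven delivery.

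Finally, new envelope lists would achieve little. Trial status has recruitment running since February 2018, due to end in June 2021 and possibly in December 2021, and the article appeared in July 2021.

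**Conclusion.** The point holds as a moderate-to-low matter of efficiency. The article acknowledges therapist differences and then names a model that ignores the factor carrying them. The loss is precision: standard errors about 2.6%, 5.4% or 11.8% wider if hospital explains 5%, 10% or 20% of the relevant variance under balanced allocation, and next to nothing at 2%. These shares are assumptions, as are the equal hospital sizes and the 0.65 SD difference. The conclusion that neither way of keeping the lists inflates the type I error needs no particular share within the range examined. The change is worth making because it costs almost nothing, not because the trial would mislead without it.

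**What to change.** In Statistical analysis, add hospital (four levels) as a fixed between-subject factor, together with hospital x time, to the mixed models for the primary and secondary outcomes. If the rank-based fallback is used, replace the Kruskal-Wallis comparison between groups with a version stratified by hospital. Friedman's test works within participants and needs no such change. Report the number of participants per arm in each hospital, and state in Randomization and blinding whether the lists were kept per hospital.

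Keep the limitation in the Discussion, and do not change the allocation method this late in recruitment.

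The cost with all 120 analysed is 3 of 120 - 3 = 117 between-subject degrees of freedom and, for hospital x time over five assessments, 3 x 4 = 12 of 117 x 4 = 468 within-subject degrees of freedom. No new data are needed, and the change should be fixed in writing before the analysis begins.
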